## Abstract

**Background:**

Women with *BRCA1/2* mutations have a higher risk of developing breast and ovarian cancer compared to women of the general population. Various preventive options are available to deal with the increased risk of developing cancer. These include intensified breast cancer screening and risk-reducing bilateral mastectomy and salpingo-oophorectomy. The choice of a preventive option can lead to increased decisional conflict. To support these women in their decision-making process, two evidence-based decision aids were developed in an upstream research process and adapted to the German healthcare context. These will be evaluated within a randomised controlled trial (RCT) in terms of their effects on decision-making, women’s level of information and psychological outcome variables.

**Methods:**

A sample of 310 women carrying *BRCA1/2* mutations (A) without a history of cancer or (B) with a history of unilateral breast cancer who have received post-test genetic counselling will be enrolled. Upon study consent, women will be randomly assigned to either the intervention or the control group. All participants will receive standard care including a physician’s letter summarising the counselling content. After baseline data collection (t0), the intervention group receives the respective decision aid while the control group receives standard care only. The primary outcome variable assessed at a 3-month follow-up (t1) is the change of extent in decisional conflict (measured with the Decisional Conflict Scale). Secondary outcome variables comprise the stage of decision-making, self-reported symptoms of anxiety, depression and stress due to the genetic test result, and knowledge regarding cancer risks and preventive options. At t1, the extent of preparation for decision-making and acceptability of the decision aids will also be examined. Another secondary outcome variable assessed at 6-month follow-up (t2) is the extent of decision regret.

**Discussion:**

These will be the first decision aids available for *BRCA1/2* mutation carriers in Germany to be evaluated regarding their effectiveness and acceptability in clinical use within an RCT. Subsequently, they are to be integrated into the care concept of the centres of the German Consortium for Hereditary Breast and Ovarian Cancer and the affiliated breast centres.

**Trial registration {2a}:**

DRKS DRKS00015823. Retrospectively registered on 14 June 2019

## Administrative information

Note: The numbers in curly brackets in this protocol refer to SPIRIT checklist item numbers. The order of the items has been modified to group similar items (see http://www.equator-network.org/reporting-guidelines/spirit-2013-statement-defining-standard-protocol-items-for-clinical-trials/).

## Introduction

### Background and rationale {6a}

Women with a pathogenic germline mutation in the *BRCA1* or *BRCA2* gene face a high risk of developing breast cancer (BC) and ovarian cancer (OC). The average cumulative life-time risk for BC increases with age [1, 2], reaching about 70% by the age of 80 [1]. The average cumulative lifetime risk for OC is around 44% (*BRCA1* mutation) and 17% (*BRCA2* mutation) [1]. Compared to women affected by sporadic BC or OC, *BRCA1/2* mutation carriers without a history of cancer, in the following referred to as ‘previvors’ [3], develop BC or OC about 20 years earlier in their life. Those with a history of unilateral BC, in the following referred to as ‘survivors’ [4], face an average cumulative 20- to 25-year risk of contralateral BC of about 40 to 44% (*BRCA1* mutation) or around 26 to 33.5% (*BRCA2* mutation) [1, 5].

Newly diagnosed *BRCA1/2* mutation carriers are offered various preventive options to counter their increased cancer risks. These include an intensified breast cancer screening programme for previvors or an intensified breast cancer screening and aftercare programme for survivors and risk-reducing surgeries of the breasts and the adnexa for both groups. Intensified breast cancer screening (breast magnetic resonance imaging (MRI), breast ultrasound and mammography) enables BC to be detected at an early, potentially curable stage in 85% of cases [6], but does not reduce the risk of developing BC. Women who opt for screening in the first place can postpone their final decision to have surgery. Due to the limited specificity of the MRI, screening often yields false-positive results [6] which can lead to further often more invasive diagnostic tests (e.g. re-imaging or breast biopsies) which may later prove unnecessary and may trigger transient anxiety in women [7]. In contrast, risk-reducing bilateral mastectomy significantly decreases the risk of developing BC [8] for previvors and provides a survival benefit to *BRCA1* mutation carriers [9]. Risk-reducing contralateral mastectomy lowers the risk of contralateral BC and reduces overall mortality in survivors [10]. However, removal of the breasts is an irreversible decision that affects physical integrity and requires further decisions, e.g. which form of surgery or whether and, if so, which breast reconstruction the woman would prefer. For survivors, the decision-making process may be even more complex because they may face competing risks (e.g. risk of BC recurrence on the affected side) that may have to be weighed against the benefits of risk-reducing surgery on the non-affected side.

In the absence of an effective screening method for the adnexa [11–14], the only preventive option to counter the risk of OC is risk-reducing bilateral salpingo-oophorectomy. It reduces both the risk of OC [15] and the overall and OC specific mortality [16]. However, consequences include the definite loss of fertility and possible premature menopause; the latter can cause menopausal symptoms such as hot flashes, as well as long-term consequences such as cardiovascular disease and osteoporosis [17].

Each preventive option is accompanied with distinct advantages and disadvantages that each mutation carrier will judge and weigh individually depending on her personal experiences, values and preferences. The same applies to the several options of breast reconstructions after mastectomy, to family planning or to steps to be taken to treat undesired effects of an option [18]. For example, to counter the negative consequences of surgical menopause after a risk-reducing bilateral salpingo-oophorectomy, temporary hormone replacement therapy might be considered for premenopausal women [11]. Hence, *BRCA1/2* mutation carriers face several so-called preference-sensitive decisions [19, 20]. These can lead to considerable decisional conflicts that can be associated with delays of decisions, dissatisfaction, decision regret or blaming of healthcare providers [21–26]. These negative consequences might be further complicated by lacking knowledge and understanding of the individual risk constellation and available options or by personal stressors and psychosocial, family and/or psychological factors [20, 26–29].

In order to support *BRCA1/2* mutation carriers during their complex decision-making process in choosing a preventive option and the right time to do so, a number of supportive tools, in particular, decision aids (DAs), have been developed internationally [30–36]. A systematic review on DAs for women with *BRCA1/2* mutations identified four RCTs and one pretest-post-test study that assessed the effectiveness of DAs on decision-, knowledge- and health-related criteria. The analysis showed that DAs support these women most likely by improving decision-related outcomes: Women who received a DA experienced lower decisional conflict were more likely to come to a decision and were more satisfied with the decision made compared to women who did not receive a DA [37]. Favourable effects of DAs on decision-related factors as well as on knowledge are reported by a previous Cochrane Review that analysed 105 RCTs involving a total of 31,043 participants with regard to the effects of DAs on patients facing treatment or screening decisions across different indications. High-quality evidence was found for the following effects: DAs improve knowledge about the available options, lower decisional conflicts resulting from the feeling of not being informed and support clarification of values and preferences of the addressees [38].

In Germany, following receipt of the genetic test result, women with a pathogenic *BRCA1/2* mutation receive personalised counselling from a medical specialist at one of the specialised GC-HBOC centres or their affiliated breast centres. The post-test genetic counselling and care concept (in the following referred to as ‘standard care’) includes detailed non-directive information on the women’s mutation status, their individual risk prediction, risks and benefits of the available risk-adapted prevention options and their consequences [11, 39–41], provision of written information, e.g. on self-help or psychological support options, along with a physician’s letter summarising the contents of the consultation. So far, no additional structured intervention is used to provide women carrying *BRCA1/2* mutations with targeted support for making high-quality decisions defined as being informed by the best available scientific knowledge and based on the women’s values and preferences [42, 43].

For this reason, two evidence-based DAs (one for previvors (DA-A), one for survivors (DA-B) with *BRCA1/2* mutations) that correspond to the evidence-based guidelines and consented procedures in the German healthcare system were developed in an upstream research process [44]. The development of the DAs followed a structured, quality-controlled procedure according to the International Patient Decision Aid Standards Collaboration [45–47]. Both DAs follow the same structure and share the same content for all aspects that are valid for both target groups (e.g. information on genetic mutations, methods of breast cancer screening). Yet, they differ in aspects where the respective target group needs and/or wishes distinct information. For example, previvors need information on the risk-reducing bilateral removal of healthy breasts, while survivors need information on BC in the affected breast and on the risk-reducing removal of the non-affected breast. Before the newly developed DAs can be incorporated into standard care, it is required to evaluate these in terms of their effectiveness and acceptability in clinical use [45, 48]. In order to fulfil this final quality criterion, the DAs will be evaluated in the randomised controlled trial (RCT) described here in detail.

### Objectives {7}

The aim of this study is to evaluate two newly developed evidence-based DAs for women with pathogenic *BRCA1/2* mutations in Germany with regard to their effectiveness on decision-, psychological- and knowledge-related factors in clinical use and their acceptability with the addressees. We hypothesise that the use of these DAs on top of standard care will reduce the extent of decisional conflict regarding the choice of a preventive option compared to standard care alone (primary outcome). Furthermore, it will be examined whether the use of the DAs can reduce possible symptoms of anxiety, depression or psychological strain associated with the genetic test result, the risk of BC and OC and the available preventive options. Lastly, we hypothesise that at 6-month-follow-up, the intervention group (IG) will feel less regret regarding the choice made compared to the control group (CG).

### Trial design {8}

The trial is designed as a monocentric randomised controlled parallel-group superiority trial with a 1:1 allocation ratio.

## Methods

The study protocol is based on the Standard Protocol: Recommendations For Intervention Trials (SPIRIT 2013 Statement) [49].

### Study setting {9}

All participants will be recruited by the medical specialist team supported by a study nurse (recruiting team) at the Centre for Familial Breast and Ovarian Cancer at the University Hospital of Cologne (recruiting institution). All data will be collected and analysed by the research team consisting of physicians, healthcare researchers, and a statistician at the Institute for Health Economics and Clinical Epidemiology at the University Hospital of Cologne (data evaluation institution).

### Eligibility criteria {10}

All participants must meet the inclusion criteria for genetic testing according to the German Consortium for Hereditary Breast and Ovarian Cancer (GC-HBOC) [50] and have undergone a genetic testing. Included in the study are women with a positive genetic test result for a pathogenic *BRCA1*/2 mutation who have received post-test genetic counselling and have not yet made a final decision on at least one preventive measure. This includes both mutation carriers immediately after the post-test genetic counselling and those later on after post-test genetic counselling who have initially decided to participate in the intensified breast cancer screening (and aftercare) programme but do not yet know, when and for which alternative they will finally opt.

Further inclusion criteria are as follows:
(A) Not affected by cancer or (B) affected by unilateral BC (stage I, II or III)Age 18 to 70 yearsNo medical reasons against possible risk-reducing surgeriesGiven written consent to participate in the studySufficient knowledge of the German language

Exclusion criteria are as follows:
Affected by advanced BC, e.g. local recurrence or distant metastasisAffected by ovarian cancer or other types of cancer other than unilateral BCAge under 18 years and over 70 yearsMedical reasons against possible risk-reducing surgeryNot able to give informed consent/not given informed consent to participate in the studyInsufficient knowledge of the German language

### Consent to participate {26a}

The recruiting physicians will obtain the informed written consent of potential trial participants after they have been informed about the study and are willing to participate. Informed consent will be obtained from all study participants.

### Additional consent provisions {26b}

In the consent form, the participants will also be asked to agree that in the event of withdrawal from the study, their data collected up to that point may be processed. No further consent provisions will be requested.

### Interventions

#### Choice of comparators {6b}

The participants of the CG will receive standard care. Standard care was chosen as the comparator, because it is offered for all women with pathogenic *BRCA1/2* mutations seeking advice by the specialised GC-HBOC centres as part of post-test genetic counselling and is currently considered the gold standard.

Standard care in the GC-HBOC centres is as follows: In a medical non-directive consultation mutation, carriers receive detailed individual information on their genetic test results, their lifetime, age- and/or time-dependent risks of BC and OC and the risk-adapted preventive options available to them. In addition, further written information may be provided, e.g. on the German self-help organisation BRCA network (BRCA-Netzwerk e.V.) or on psychological counselling options. Following a detailed physician’s consultation, each woman receives a personal physician’s letter summarising the contents of her consultation by regular mail. This includes information about the identified mutation, the calculated individual risks for breast and ovarian cancer, the intensified breast cancer screening programme with pros and cons, the risk-reducing surgeries of the breast and ovaries and fallopian tubes with pros and cons, possible further cancer risks, the significance of the genetic test result for a possible desire to have children, the probability of passing on the mutation to the offspring and a summary of the result of the counselling interview.

#### Intervention {11a}

Participants in the IG will also receive standard care as described above. After the return of the baseline questionnaire (t0), participants of the IG will be sent the DAs as a brochure by regular mail. Participants of the CG will not receive a DA.

#### Criteria for discontinuing or modifying allocated interventions {11b}

No known unfavourable side effects of the implementation of DAs are reported in the literature. Nevertheless, all participants will be offered to set up an appointment with the clinical psychologist at the recruiting institution in case stressful feelings or thoughts will be coming up. They will also be offered an additional specialist appointment at the centre if the need to clarify further issues arises. Participants will be informed that participation is completely voluntary and that they can leave the study at any time without giving any reason or having to fear negative consequences.

#### Strategies to improve adherence to intervention protocols {11c}

Participants of the IG are encouraged to read through the DAs and engage with them by filling out the attached work sheets and discuss its contents with persons of their confidence. No special strategy was defined to facilitate the use of the DAs. To support physicians’ assistance to recruit eligible participants into the study, a study nurse will be involved. The study nurse will review the patient files with upcoming appointments every day and will place the enrolment documents in the files of eligible women.

#### Concomitant care or interventions {11d}

Not applicable. No concomitant care or interventions are planned. No concomitant care or interventions are explicitly prohibited.

### Outcomes {12}

Baseline measures at t0 will be obtained within 2 weeks after enrolment in the study, t1 measures 3 months and t2 measures 6 months after enrolment (see Table 1). At baseline (t0), the following variables will be collected: decisional conflict as measured with the Decisional Conflict Scale (DCS) [51], stage of decision-making as measured with the Stage of Decision Making Scale, SDM-S [52], anxiety and depressive symptoms as measured with the Hospital Anxiety and Depression Scale, HADS [53, 54], impact of genetic test result as measured with the Impact of Event Scale-Revised, IES-R [55] and knowledge criteria as measured with a set of fifteen knowledge questions.

**Table 1 Tab1:**
[figure not shown]
Outcome parameters and time points for outcome measurements

The primary outcome at 3-month follow-up (t1) is the change in the extent of decisional conflict measured with the DCS. Secondary outcome variables at t1 include changes in SDM-S, HADS, IES-R and knowledge. Additionally, at t1, the items addressing the preparation for decision-making as measured with the Preparation for Decision Making Scale (PrepDMS) [56, 57] and the acceptability of the DAs compared to control by the participants as measured with an acceptability instrument [30, 58] are collected. Secondary outcome variables at t2 comprise SDM-S, DCS, HADS and the extent of regret for the decision made as measured with the Decision Regret Scale (DRS) [59]. It is possible that no final decision has been made at t2 or that the decisions made at t2 are only temporary.

The evaluation instruments are described below.

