#### Decision regret

To assess the participants’ level of distress and regret in terms of the final decision made, the Decision Regret Scale (DRS) [21, 59, 66] is used. It consists of five items to be rated on a 5-point Likert scale (from 1 = strongly agree to 5= strongly disagree). The instrument was validated in a sample of BC patients and showed good internal consistency with a Cronbach’s alpha = 0.81 to 0.92. It is strongly negatively correlated with decision satisfaction and overall quality of life and positively correlated with decisional conflicts [21]. The DRS is administered at t2.

The outcome parameters and time points for outcome measurements are listed in Table 1.

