## Statistical methods

### Analysing primary and secondary outcomes {20a}

Analysis of the baseline data (t0) will be done to ensure the comparability of the two study groups. Outcomes are measured at t1 and t2. All primary and secondary effectiveness variables will be described by statistical characteristics values. Continuous data will be described by mean, standard deviation, median, minimum and maximum. Categorical data will be described by using frequencies and percentages. The number of non-missing values will also be given.

The primary outcome at t1 is decisional conflict. The mean differences of the primary outcome between both groups will be compared using the independent *t-*test in case of normal distribution. In addition, the mean differences in the score within the groups between t0 and t1 will be compared using a dependent *t-*test. Non-parametric tests will be used in case of non-normal distribution. Secondary outcomes comprise the mean differences in scores of the stage of decision-making, stress, anxiety and depressive symptoms between t0, t1 and t2. A further secondary outcome measured at t2 is the regret of the decision. For these analyses, a dependent respectively independent *t-*test will be used in case of normal distribution, non-parametric tests will be used in case of non-normal distribution. Data will be analysed by using IBM SPSS Statistics for Windows, version 27.0 (IBM Corp: Armonk, NY) and R [71]. An alpha level of 0.05 is considered significant in all statistical tests.

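### Decision regret at t2 is planned as an intention-to-treat comparison of all randomised women, but it refers to a final decision that some will not have made and that the aid is expected to influence

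*Protocol article*

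**What the plan says.** Objectives {7} states a between-arm hypothesis: at 6 months the intervention group (IG) will regret its choice less than the control group (CG). The section Decision regret says the scale assesses the "level of distress and regret in terms of the final decision made" and is given at t2; it does not say who is to complete it. Under Outcomes {12}, below Table 1, the protocol accepts: "It is possible that no final decision has been made at t2 or that the decisions made at t2 are only temporary".

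Analysing primary and secondary outcomes {20a} adds: "A further secondary outcome measured at t2 is the regret of the decision". It assigns a dependent or independent t-test, or non-parametric tests if the data are not normal. Regret is measured once, so only an independent comparison of arms is possible. Definition of analysis population {20c} puts every analysis on an intention-to-treat basis in all randomised patients, with no imputation.

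Three further statements bear on who will have decided by t2:
- Eligibility criteria {10}: entrants "have not yet made a final decision on at least one preventive measure".
- Background {6a}, on screening: "Women who opt for screening in the first place can postpone their final decision to have surgery".
- Background {6a}, on a systematic review of earlier aids: women given an aid "were more likely to come to a decision and were more satisfied with the decision made compared to women who did not receive a DA".

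Stage of decision-making (SDM-S; category 4 means a choice has been made) is itself a secondary outcome, collected at t0, t1 and t2.

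**The concern.** Regret needs a decision to refer to. Having decided by t2 is an event after randomisation, and the protocol gives reason to expect it to be more common with the aid. Women who have decided in one arm may therefore differ from those who have decided in the other in ways unrelated to how the aid affects regret. A test on their scores would nevertheless be read as a randomised effect, because the hypothesis and the population statement are worded that way. A difference could appear, or a real one be hidden, because different women had decided in each arm.

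**Working it through.** **Step 1: do the statements fit together?** Two cases cover the women without a final decision at t2.

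- *They leave the DRS blank.* Without imputation they drop out of the test. The comparison is then between deciders in each arm, a subset defined after randomisation, and not among all randomised women.
- *They answer it.* The all-randomised population is nearer to being met, but their score rates no choice or a provisional one. The measure then means different things for different women, in proportions that may differ by arm.

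Neither case yields a randomised comparison of regret about a final decision.

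**Step 2: the plan's own figure.** Sample size {14} covers the primary outcome only; no figure is given for regret. With d = 0.3, one-sided 5% and 80% power, the normal approximation is 2 × (1.645 + 0.842)² / 0.3² = 137.4, so 138. The exact t-test gives 138.07, rounded up to 139 per group. Then 139 / 0.9 = 154.4, so 155 per group and 310 in total. The plan's numbers reproduce. I use 139 per arm as the number followed up.

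**Step 3: how large could selection be?** This covers the first case only. The inputs below are assumptions; the document gives neither shares nor correlations.

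- The aid has no effect on any woman's regret, which has SD 1.
- A woman has decided by t2 if a normal readiness score exceeds a threshold c, set so that a share p of her arm has decided.
- Readiness has correlation r with low regret, the same in both arms.

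Mean regret among deciders is then −r × φ(c)/p, so the false gap (IG minus CG) is r × [φ(c_CG)/p_CG − φ(c_IG)/p_IG]. Positive means more regret with the aid. The standard error, taking SD as 1, is √(1/n_IG + 1/n_CG).

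*60% (IG) versus 40% (CG) decided:* φ(c)/p is 0.386/0.60 = 0.644 and 0.386/0.40 = 0.966, a difference of 0.322. Deciders number 139 × 0.60 = 83.4 and 139 × 0.40 = 55.6, so SE = 0.173.

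*55% versus 45%:* 0.396/0.55 = 0.720 and 0.396/0.45 = 0.880, a difference of 0.160. Deciders number 76.5 and 62.6, so SE = 0.170.

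| Decided, IG vs CG | r | False gap (SD) | Two-sided rejection, nominal 5% |
|---|---|---|---|
| 60% vs 40% | 0.2 | 0.064 | 6.6% |
| 60% vs 40% | 0.4 | 0.129 | 11.5% |
| 60% vs 40% | 0.6 | 0.193 | 20.0% |
| 55% vs 45% | 0.2 | 0.032 | 5.4% |
| 55% vs 45% | 0.4 | 0.064 | 6.6% |
| 55% vs 45% | 0.6 | 0.096 | 8.7% |
| 50% vs 50% | any | 0 | 5.0% |

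**Step 4: direction.** With these signs the gap runs against the aid. At 60% versus 40%, significance in favour of the aid falls to 1.0%, 0.3% and 0.1% for the three correlations, against a nominal 2.5% in that tail. The same bias can mask benefit: at r = 0.4 a true benefit of 0.30 SD would show as 0.30 − 0.13 = 0.17 SD. A correlation of the opposite sign reverses all of this.

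**The case against.** The strongest reply is that the protocol never restricts the DRS to women who have decided, and expects some to hold temporary decisions. A reader might infer that regret will be scored only in deciders; the text does not say so. It is also true that entrants need be undecided on only one measure, so a woman may already have another choice to rate, and the undecided group may be small. These points stand, and the conclusion is therefore put as two cases, with figures for only one.

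A reader might also take the 20% as the chance of wrongly declaring the aid beneficial. The model does not support that: nearly all of those rejections go against the aid. The shares and correlations are assumed, and a 20-point difference in the share deciding is large.

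Some of the remedy is already in place, since the SDM-S is collected at t2 and the possible lack of a decision is disclosed. Detail on who completes a scale may also sit in a fuller document. But this article itself fixes the hypothesis, the test, the population and the missing-data rule, and concedes the difficulty without adjusting any of them. The limitations in the Discussion cover non-use, contamination, unblinding and non-response, but not this.

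**Conclusion.** The point holds in this form: for decision regret, the hypothesis, the test and the all-randomised population do not fit an outcome that some women will not have. Whether undecided women answer or not, the planned comparison lacks the protection of randomisation that its wording implies. This follows from the text and needs no assumed number.

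The size and direction of bias cannot be derived from the document. Under the assumed model the false gap is 0.06 to 0.19 SD at 60% versus 40% decided (two-sided rejection about 7% to 20%), 0.03 to 0.10 SD at 55% versus 45% (about 5% to 9%), and nil at equal shares with equal selection. It would be wrong to infer that the plan is biased towards the aid, or that the trial's main conclusion is at risk: regret is secondary, and decisional conflict at t1 is untouched. The change is one that should be made.

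**What to change.** - **{20a}:** pre-specify the between-arm comparison of the proportion in SDM-S category 4 at t2 as the randomised decision outcome at that visit. The section at present plans mean differences in the stage score.
- **{20a}:** report DRS by arm among women in category 4 at t2, labelled descriptive and non-randomised, beside the share decided in each arm. Category 4 is a single item and does not show which of several decisions was rated; the report should say so.
- **{7} and {20c}:** reword the regret hypothesis and the intention-to-treat statement to match.
- **Optional:** a sensitivity analysis with bounds, or for women who would decide in either arm. It needs further assumptions, such as that the aid stops no woman from deciding, and is not essential for a secondary outcome.

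The cost is wording and one table. The SDM-S at t2 is already collected, so closed recruitment is no obstacle, but the change should be fixed before t2 results by arm are seen. The regret claim becomes weaker.
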